# Retroclavicular approach vs infraclavicular approach for plexic bloc anesthesia of the upper limb: study protocol randomized controlled trial

**DOI:** 10.1186/s13063-017-2086-1

**Published:** 2017-07-21

**Keywords:** Regional anesthesia, Brachial plexus anesthesia, Coracoid approach, Retroclavicular approach

## Abstract

**Background:**

The coracoid approach is recognized as the simplest approach to perform brachial plexus anaesthesia, but needle visualization needs to be improved. With a different needle entry point, the retroclavicular approach confers a perpendicular angle between the ultrasound and the needle, which theoretically enhances needle visualization. This trial compares these two techniques. The leading hypothesis is that the retroclavicular approach is comparable to the infraclavicular coracoid approach in general aspects, but needle visualization is better with this novel approach.

**Methods:**

We designed a multicentre, randomized, non-inferiority trial. Patients eligible for the study are older than 18 years, able to consent, will undergo urgent or elective upper limb surgery distal to the elbow and are classified with American Society of Anaesthesiologists risk score (ASA) I-III. They will be excluded if they meet contraindicated criteria to regional anaesthesia, have affected anatomy of the clavicle or are pregnant. Randomization will be done by a computer-generated randomization schedule stratified for each site and in 1:1 ratio, and concealment will be maintained with opaque, sealed envelopes in a locked office. The primary outcome, the performance time, will be analyzed using non-inferiority analysis while secondary outcomes will be analyzed with superiority analysis. Needle visualization will be ranked on a Likert scale of 1–5 that is subjective and represents a pitfall. Two separate persons will rank needle visualization to compensate this pitfall. According to previous studies, 49 patients per group are required for statistical power of 0.90 and one-sided type I error of 0.05.

**Discussion:**

The conduct of this study will bring clear answers to our questions and, if our hypothesis is confirmed, will confer an anatomic alternative to difficult coracoid infraclavicular brachial blocks or could even become a standard for brachial plexus anaesthesia.

**Trial registration:**

ClinicalTrials.gov, NCT02913625. Registered on 12 September 2016.

**Electronic supplementary material:**

The online version of this article (doi:10.1186/s13063-017-2086-1) contains supplementary material, which is available to authorized users.

## Background

Regional anaesthesia (RA), or the action of blocking nerve conduction temporarily, has been conducted since the beginning of surgical interventions described on humans. With time, techniques evolve, become safer, easier to perform and more effective. When compared to general anaesthesia, RA may offer better outcomes. RA has been linked with reduced postoperative pain, reduced need of postoperative opioids and reduced recovery time in patients undergoing orthopaedic surgery [1, 2]. Thus, when it comes to limb surgery, regional anaesthesia is a very interesting approach.

Simplicity, rapidity and safety of ultrasound-guided (USG) techniques, have propelled the interscalene, supraclavicular, infraclavicular (coracoid) and axillary block as the most popular techniques for shoulder surgery and upper limb surgery [3–6]. Many other approaches have previously been described for upper limb anaesthesia, but their popularity decreased when simpler and safer techniques were reported.

When it comes to elbow and distal upper limb surgery, the infraclavicular approach (ICB) offers many advantages. A Cochrane review reports that coracoid ICB offers a lower likelihood of tourniquet pain, more reliable blockade of the musculocutaneous nerve when compared to a single-injection axillary block, and significantly shorter block performance time compared to multi-injection axillary and mid-humeral blocks [3]. Also, coracoid ICB has been shown to be the easiest way to provide anaesthesia for the brachial plexus [7] because positioning of the operative limb is less painful, the coracoid process is easy to locate and the technique is easy to learn and master [6]. Furthermore, ICB is recommended as the standard of training for anaesthesia residents because of its simplicity and efficiency [7].

Because a steep-angle needle-ultrasound (US) beam is often required, needle visualization remains a challenge in coracoid ICB, particularly when the needle approaches the neurovascular bundle [8, 9]. Because the needle entry point is different, the recently described retroclavicular (RCB) approach offers an almost perpendicular angle between needle and the US beam [10]. This technique has already been described as efficient, rapid, safe and simple to perform in both a recent study [11] and a recent case series [12]. As such, following the Standard protocol items: recommendation for interventional trials (SPIRIT) clinical trial design recommendations (see Additional file 1) [13], our hypothesis is that when comparing RCB with coracoid ICB for upper limb surgery, both techniques will offer similar outcomes except for needle visibility. We believe that the almost perpendicular needle-US beam angle in RCB will provide superior needle visibility to coracoid ICB.

### Objectives

Our general objective is to make a formal comparison between RCB [10, 11] and coracoid ICB for brachial plexus anaesthesia. This study will delineate the differences between the two techniques. Our aim is to compare both techniques in terms of scanning time, needling time, total anaesthesia time, needle visibility, block needle passes, block success and early and late complications. We made the hypothesis that, while providing similar efficacy and better needle visualization than coracoid ICB, the time taken to perform RCB will not exceed the time taken to perform its comparator [3].

## Methods

### Participants, interventions and outcomes

#### Trial design

This study is designed as a prospective, randomized, non-inferiority trial. Two groups of non-consecutive patients will be randomly assigned to either RCB or coracoid ICB. This study will be carried out in two different centres simultaneously.

#### Study setting

The multicentre trial will be conducted in two university hospitals (Centre hospitalier universitaire de Sherbrooke (CHUS) Hôtel-Dieu/Fleurimont in Sherbrooke city and Centre Hospitalier de l’Université Laval [13] in Quebec city).

#### Eligibility criteria

##### Inclusion criteria

Patients eligible for the study must comply with all of the following at randomization:Elective or urgent surgery of the hand, wrist, forearm or elbowAge >18 yearsAmerican Society of Anesthesiologists (ASA) class I-IIIAble to provide valid written consentMinimum body weight of 50 kg, regardless of body mass index (BMI)

##### Exclusion criteria

Patient refusalPrevious surgery or gross anatomical deformity of the clavicleSystemic or local infection at the needle entry pointCoagulopathySevere pulmonary conditionLocal anaesthetic allergyPre-existing neurologic symptoms in the ipsilateral limbPregnancySurgical request for an indwelling catheter for postoperative analgesia

Enrolment in another study is not a contraindication as long as both protocols can be applied simultaneously.

#### Interventions

Blocks will be performed by anaesthesiologists experienced in US-guided regional anaesthesia or by PGY-2 to PGY-5 residents under direct supervision by an experienced anaesthesiologist. Operators will have registered a minimum of 25 USG blocks before participating in the study.

Upon arrival in the induction room, standard ASA monitoring will be installed and an 18-gauge or 20-gauge intravenous catheter will be inserted in the contralateral arm. Premedication will be given based on patient preference and the anaesthesiologist’s judgment. Patients will be placed in the supine position with the torso elevated to about 30 degrees and the head facing the opposite side. After a prescan and US parameter optimization, the US probe will then be applied using a sterile technique. A high-frequency linear US probe (6–15 Hz Philips HD11XE Ultrasound; Philips Medical Systems, Bothell, WA, USA, 9–15 Hz Logiq P6; GE Healthcare, Mississauga, ON, Canada, or 15–6 MHz linear probe Sonosite Edge HFL50x; Sonosite Canada inc. Markham, Ontario, Canada) will be used and placed parasagittally just medial to the coracoid process and caudal to the clavicle. Short-axis visualization of the axillary vessels and of the cords will be obtained; the lung and second rib will be identified.

For the retroclavicular approach, the needle insertion point will then be found by palpating the supraclavicular fossa, just medial to the shoulder, at a point sufficiently posterior to the clavicle (generally 1–2 cm depending on morphology and the extent to which the supraclavicular fossa can be depressed) and medial to the trapezius muscle insertion point on the clavicle. This landmark is essential, as the needle will need to clear the clavicle and stay parallel to the US probe to avoid any posterior angling. From this finger position, probe rotation and alignment with the palpating finger will be perfectly achieved while keeping the axillary vessels in the short axis. Once probe rotation achieves finger-probe alignment, the needle will now aim more towards the anterior axillary line than with the coracoid ICB. For optimal imaging and technique the final probe position should rest in the delto-pectoral groove.

For coracoid ICB, the US probe will be applied in the infraclavicular fossa until good visualization of the axillary vessels is obtained and if possible, the brachial plexus cords, then the optimal approach angle and puncture point will be planned.

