##### Secondary outcome measures

Imaging time: will be measured in minutes and corresponds to the time interval between contact of the US probe with the patient skin and the acquisition of a satisfactory image.Needling time: will also be measured in minutes, from the start of the skin wheal to the removal of the block needle from the tissues.Sensory loss at 10, 20 and 30 minutes: will be assessed in the territory of the radial (lateral aspect of the dorsum of the hand), median (volar aspect of the index), ulnar (volar aspect of the fifth finger), musculocutaneous (lateral aspect of the forearm), and medial cutaneous nerve of the forearm (medial aspect of the forearm) distributions using a 3-point score, where 0 = normal sensation, 1 = diminished sensation to pinpricks (hypoesthesia), and 2 = loss of sensation to pinpricks (analgesia). The sum of five scores on a maximum of 10 will be the sensory-loss final score. An independent, blinded, research assistant will complete the sensory assessment at 10, 20 and 30 minutes.Motor block at 10, 20 and 30 minutes: motor function will be tested (0 = normal strength, 1 = weakness, 2 = paralysis) for the radial (wrist extension), median (thumb-fifth finger opposition), ulnar (fifth finger abduction), and musculocutaneous (elbow flexion) nerves. The sum of the four scores on a maximum of 8 will be the motor block final score. An independent, blinded, research assistant will complete the motor assessment at 10, 20 and 30 minutes.Success of plexus block: success is a dichotomic variable answered by yes or no. Success is defined as the completion of surgery without the need for additional LA infiltration, intravenous narcotics, or general anaesthesia. However, light sedation is allowed if deemed necessary by the anaesthesiologist. Light sedation includes midazolam 1 to 4 mg intravenously, fentanyl up to 1mcg/kg. A minimum sensory score of 9/10 will be necessary to proceed to surgery without additional LA infiltration. Patients with an overall sensory score under 9/10 at 30 min will be offered general anaesthesia or supplemental blocks.Total anaesthesia time: is measured in minutes and defined as the sum of performance time and time to achieve a minimum sensory score of 9/10. It is the time for readiness for surgery.Number of block needle passes: is defined as a unit of 1, 2, 3, etc., and is the number of times the block needle will have to be realigned on the skin in order to achieve its final positioning goal under the axillary artery.Needle visualization: procedures will be videotaped and reviewed simultaneously after study completion by 2 independent anaesthesiologists skilled in US-guided regional anaesthesia using a 5-point Likert scale to rate needle visibility (1 = very poor, 2 = poor, 3 = fair, 4 = good, 5 = very good). Needle visibility will be evaluated twice. First, for RCB, assessment will be made when the needle tip is seen 1 cm after crossing the clavicle acoustic shadowing. For the coracoid ICB, the first assessment will be at a needle tip depth of 1 cm. The second needle visibility assessment will be immediately before the local anaesthetic injection, when the visibility is theoretically optimized.Needle angle: using the same videotape that we used for the evaluation of the needle visibility, we will note the angle between the needle and the upper side of the ultrasound image. It will be a continuous outcome ranging from 0 to 90 degrees.Neurostimulation use: neurostimulation is accepted if needed. However, its use other than for a safety sentinel (defined by <0.3 mA) will be recorded for subsequent analysis. It will be a dichotomous outcome.Pain during the procedure: immediately after block completion, patients will be asked to rate their discomfort associated with the procedure using a 10-cm visual analogue scale (0 = no pain, 10 = worst pain imaginable) by an independent and blinded outcome assessor.Early and late complications: the incidence of needle-induced paresthesia, vascular puncture, Horner syndrome, dyspnea, and symptoms of LA toxicity will be noted. All patients will be contacted 48 hours after surgery to ask for any delayed complications, such as dyspnea, paresthesia, weaknesses, pain at the puncture site or haematoma. Patients with complications will be followed up by our research group and a consultation in neurology may be sought.

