## Methods

### Assignment of interventions

#### Allocation: sequence generation

Participants will be randomly assigned to either the control or experimental group with a 1:1 allocation ratio as per a computer-generated randomization schedule stratified by sites using permuted blocks of random sizes. The block sizes will not be disclosed, to ensure concealment. Stratification by site will be of particular interest because in this current pre-trial state, one centre mostly uses the retroclavicular approach while the second one uses the infraclaivuclar approach.

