#### Blinding (masking)

In this trial, only the outcome assessor for the motor block and sensory block will be blinded. For obvious reasons, it is not possible to blind the anaesthesiologist performing the block. Moreover, the current setup at the included hospitals does not allow the blinding of the anaesthesiologist supervising the surgery. Thus, the anaesthesia team in the case of block failure will not be blinded. Patients will not be blinded either, as we opted not to fake a plexus block with another needle entry point for organizational reasons and to avoid patient discomfort. However, the primary outcome of performance time should not be affected by patient blinding. Considering that the anaesthesiologist will not be blinded, we did not think it necessary to blind the statistician as, even if blinded, the risk of contamination would be too high.

Discomfort during the procedure and the quality of the motor block and sensory block at 10, 20 and 30 minutes will be assessed by a blinded investigator. Another anaesthesiologist, resident or respiratory therapist will be in charge of evaluating sensory and motor function with pre-established indications to ensure competency. To reinforce blinding, chlorhexidine will be applied over the two theoretical needle entry points and two bandages will be applied.

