#### Data management

The patient file number and any additional data allowing patient recognition will be gathered in a different and unique Microsoft Excel file. Every patient will be attributed a number that will correspond to the number in the other data file. These personal data will be on a different locked computer, kept in a locked room at the hospital. These data will be directly transferred from the hand-written form to the locked computer by a research member and will never transit by mail or the Internet. Once the sensitive data are entered onto the computer, any hand-written form allowing participant recognition will be destroyed to avoid the data being divulged. Only research members will have access to the computerized data.

Non-sensitive data will be kept in an Excel folder with a number corresponding to the sensitive data number. A research member will transfer the collected data from the hand-written document to the computerized database. The hand-written document will be kept in case of future need. Back-up data will be kept on the personal computers of the main authors to allow statistical analysis. No related processes to promote data quality will be used, as only research members will be responsible for data transfer from the hand-written document to the computer database. Blocks will be videotaped by recording the screen of the ultrasound device. Patients will not be recorded during these procedures and there will not be any possibility of recognizing the person undergoing the block. Data will be shared by the authors via a password-secured file (Dropbox®) that is only accessible to authors of the study. As soon as the videos are shared between recruiting centres, the videos will be stored in a separate file on the same locked computer as used to store the rest of the information collected.

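### Three ultrasound systems are permitted, but the stated test of needle visibility uses neither the machine nor the randomisation stratum (site); settling, recording and stratifying by machine would be a cheap improvement

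*Protocol article*

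**What the plan says.** All references are to the protocol article.

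- **Equipment.** Interventions permits three high-frequency linear systems: a Philips HD11XE, then "9–15 Hz Logiq P6; GE Healthcare, Mississauga, ON, Canada, or 15–6 MHz linear probe Sonosite Edge HFL50x". It does not say which hospital owns which system, who chooses, or when.
- **Centres.** Study setting: "The multicentre trial will be conducted in two university hospitals". One is in Sherbrooke, with Hôtel-Dieu and Fleurimont both named, and the other is in Quebec City.
- **Randomisation.** The schedule is 1:1 and "stratified by sites using permuted blocks of random sizes". Machine is not a stratum.
- **Measurement of visibility.** Data management: "Blocks will be videotaped by recording the screen of the ultrasound device". Under Secondary outcome measures, "procedures will be videotaped and reviewed simultaneously after study completion by 2 independent anaesthesiologists", on a five-point scale and at two moments of the procedure.
- **Imaging time.** It ends when the operator has an adequate image, and it is one of the two components of the primary outcome, performance time.
- **Blinding.** The article states that "it is not possible to blind the anaesthesiologist performing the block".
- **Analysis.** Statistical methods names a non-inferiority test of means for performance time, and t, Mann-Whitney, chi square or Fisher tests for the secondary outcomes. BMI is the only further factor examined, in a subgroup analysis. Neither site nor machine enters any stated test.

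**The concern.** For needle visibility the ultrasound system is part of the measuring instrument: raters see only what that machine displayed. The article fixes other equipment closely. It names one needle and removes from the analysis any patient treated with another, but it leaves the imaging system open among three manufacturers. Better visibility is the superiority claim that the Abstract and Background put forward, so the handling of the instrument matters for that claim.

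Two things could follow. Differences between machines, and between sites, go into the error term of an unadjusted test and cost precision. And if an operator who knows the allocation also picks the machine, a difference between machines could be mistaken for a difference between approaches. The first follows whenever machines differ. The second needs a link between arm and machine.

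**Working it through.** **Figures in the plan.** The article gives no figure for visibility, imaging time or machine, so there is none to reproduce on this point. The only calculation is the primary sample size. With SD 138 s, margin 5% × 336 = 16.8 s, expected difference 269 − 336 = −67 s, one-sided 0.05 and power 0.90:

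n = 2 × 138² × (1.645 + 1.282)² / (16.8 + 67)² ≈ 46.5, so 47 per group (48 with the noncentral t).

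This is close to the stated 49. It has no bearing on the machine question except to give the planned 55 per group used below.

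**Assumptions not in the documents.** Two machine types, a within-machine SD of 1 Likert point, a machine effect of 0.5 or 1.0 point, and no true difference between approaches.

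**Step 1: machine independent of arm.** Bias is zero. With equal use of the two machines, the variance due to machine is 0.5 × 0.5 × effect².

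- 0.5 point: 0.25 × 0.25 = 0.0625; share 0.0625 / 1.0625 = 5.9%.
- 1.0 point: 0.25 × 1 = 0.25; share 0.25 / 1.25 = 20%.

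In information terms, 110 patients count as about 110 × (1 − 0.059) ≈ 104, or 110 × 0.80 = 88. The simulated type I error of an unadjusted t test at two-sided 0.05 was 0.049 and 0.050.

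**Step 2: machine tied to site.** Balance within site keeps the bias at zero. With 38 of the 55 in each arm assumed to be at one site, the simulated type I error was 0.045 (0.5 point) and 0.033 (1.0 point). The unadjusted test is then conservative, because it ignores a stratum that the randomisation balanced.

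**Step 3: machine related to arm (hypothetical).** Bias = difference between arms in the proportion using the better machine × machine effect. Simulated type I error, 55 per arm, unadjusted t test:

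| Difference in use | Bias, 0.5 point | Type I error | Bias, 1.0 point | Type I error |
|---|---|---|---|---|
| 10 percentage points | 0.05 | 0.055 | 0.10 | 0.08 |
| 20 percentage points | 0.10 | 0.08 | 0.20 | 0.15 |
| 40 percentage points | 0.20 | 0.17 | 0.40 | 0.47 |

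A separate simulation with rounded five-point scores and the Mann-Whitney test gave 0.17 and 0.45 at the 40-point difference, and 0.15 at 20 points with a 1.0-point effect. A test stratified by machine stayed between 0.048 and 0.059 throughout.

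**Step 4: reach into the primary outcome.** Planned imaging time is 45 s of 336 s, or 13%. That route from machine to performance time is small.

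**The case against.** The strongest reply is that an equipment list is not a licence to use any machine for any patient. The article names two Sherbrooke locations and one in Quebec City. Three locations and three systems would fit one machine per location, though the article does not say so. The machine would then follow where the patient has surgery, not the arm, and randomisation would remove the bias even if strata are centres rather than buildings. Chance imbalance is already covered by the type I error of the test. A selection rule or a field for the machine may sit in the full protocol or on the data form, neither of which is shown. Visibility is formally secondary, and using each hospital's own machines is ordinary in a multicentre trial.

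Most of this stands. A reader might infer from the open list and the unblinded operator that the visibility result will reflect the machine rather than the approach, with false-positive rates of 17% to 47%. The documents do not support that. No passage links machine to arm, and those rates rest wholly on assumed splits and effects.

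The reply does not remove two things. The tests are stated, not merely left unsaid, and they omit site as well as machine. The article itself explains why site matters: before the trial, one centre mostly used one approach and the second the other. And nothing in the article settles the machine before allocation is known.

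**Conclusion.** The point holds as a modest improvement to the design and analysis, not as a demonstrated bias. If machine is independent of arm, the cost of the stated analysis is precision on visibility: about 6% of the variance for an assumed 0.5-point machine effect and 20% for 1.0 point, given a within-machine SD of 1 and equal use of two machines. If the machine were chosen with knowledge of the arm, bias would equal the imbalance times the machine effect. That route is open, but there is no evidence that it is used. The non-inferiority conclusion on performance time is not called into question.

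**What to change.** 1. **Interventions:** state that each patient's machine is settled before the envelope is opened, and record it on the existing standardised data form. For patients already enrolled (a quarter of the sample at submission), take it from the stored recording where it can be identified. In those patients the machine may have been chosen after allocation, so show the results with and without stratification by machine.
2. **Statistical methods:** compare needle visibility with a Mann-Whitney test stratified by site and machine (van Elteren).
3. **Sensitivity analysis:** give a site- and machine-adjusted analysis of imaging time and performance time. The primary test stays as it is.
4. **Reporting:** tabulate machine use by arm, so that readers can see whether the two are related.

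The cost is one sentence, one data field, a few degrees of freedom and slightly less freedom to swap machines on the day. A stratum that contains only one arm adds nothing to the stratified test, so very sparse machine-by-site cells lose some information. No extra patients or procedures are needed.
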